### Study Outcomes

#### Primary Outcome

The primary outcome of this study is to compare the proportion of study subjects who receive reperfusion within the target door-to-reperfusion times across the four care strategies. Target door to reperfusion times are 90 minutes for primary PCI intervention (door-to-balloon time) and 30 minutes for fibrinolysis (door-to-needle time)[30-32].

### Secondary Outcomes

#### Survival

Survival at 30 days and one year after episode date (brief telephone assessment) for STEMI patients

### Treatment Time Intervals

• Prehospital scene time interval defined as time from arrival at scene to departure from scene;

• Transport time interval defined as time from departure from scene to arrival at destination hospital;

• Symptom onset time interval defined as time from symptom onset reported by subject to reperfusion intervention (defined as time to drug administration or balloon inflation);

• Primary hospital reperfusion time interval defined as the time from arrival at primary destination hospital to reperfusion intervention at the primary destination (defined as time to drug administration or balloon inflation);

• PCI transfer reperfusion time interval defined as the time from arrival at primary destination hospital and transport to a PCI capable site to the reperfusion intervention at the PCI site (defined as time to drug administration or balloon inflation).

• PCI site reperfusion time interval defined as the time from arrival at PCI site to reperfusion intervention at the PCI site (defined as time to drug administration or balloon inflation)

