## Methods/Design

### Study Design

PREDICT is a prospective, population-based cohort study of four patient care strategies provided by regional EMS services to patients with chest pain and suspected ischemia.

1. 3-lead PHECG and transported to the nearest receiving ED who were not eligible for bypass based on transport time.

2. 3-lead PHECG and transported to the nearest receiving ED who were eligible for bypass based on transport time, if 12 lead PHECG was possible.

3. 12-lead PHECG and prehospital notification transported to the nearest receiving ED who were not eligible for bypass to a PCI center based on transport time.

4. 12-lead PHECG with prehospital notification and eligible for bypassing the nearest receiving ED with transport to a PCI center.

Bypass eligibility was based on transport distance of patients from their pick-up location to PCI center and the cut-off point was 60 kilometres.

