### Inclusion and Exclusion Criteria

#### Inclusion criteria

○ Patients who call 911, and are:

○ Suspected by the paramedics to have ischemic chest pain for greater than 30 minutes but less than 6 hours, and

○ 18 years of age or older

○ Experiencing chest pain that fails to resolve with nitrates given as per protocol

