### Setting

This study is set in regions of Ontario with a population of 3,043,853 served by 14 EMS services, under the medical control of 4 regional Base Hospital programs (Table 1)[27]. These regions represent 25% of the population of Ontario and 9.6% of the population of Canada. This geographic region covers 206,727 km^2 ^with variable population densities from 0.6 to 574 persons per km^2 ^representing rural, suburban, urban, and metropolis areas[27].

**Table 1 T1:** List of regional base hospital programs and emergency medical services participating in PREDICT study

Regional Basehospital Programs	Participating Emergency Medical Services (EMS)
Hamilton Health Sciences Centre for Paramedic Education & Research - Hamilton	County of Brant Ambulance Service Haldimand EMS Hamilton EMS Hamilton-Wentworth Regional Ambulance Service Norfolk EMS Six Nations Ambulance Service

North-East Ontario Regional Base Hospital Program - Sudbury	Algoma EMS Manitoulin-Sudbury EMS Sudbury EMS Sault Ste. Marie EMS Timmins EMS

Northwest Region Base Hospital Program	Superior North EMS

Sunnybrook Osler Centre for Prehospital Care - Toronto	County of Simcoe Paramedic Services, Peel Regional Paramedic Services

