### Analysis Plan

The primary outcome, and treatment time intervals, will be analyzed with one-way ANOVA and subsequent pair-wise multiple comparison procedures across the four treatment strategies. Different covariates (Table 3) will be analyzed using multiple linear regressions and they will be introduced into the model and evaluated as potential confounders. Variables will be retained if they have had an effect of 5% or greater on the coefficients for door-to-reperfusion time. Survival at 30 days and one year for STEMI patients will be analyzed as a binary outcome (Chi square) and as a survival analysis. Covariates that may affect survival will be analyzed with a Cox PH Regression Model. Adverse event rates will be analyzed with a Chi square analysis or a Fisher's exact test.

**Table 3 T3:** Analysis Plan - List of Covariates

1. Presence of cardiac catheterization lab in the primary destination hospital with the ability to perform 24-7 emergent primary angioplasty;
2. Fully affiliated teaching hospital;
3. Is the ED on Time Consideration (TC) or deferral from ambulances based on workload of acutely ill or injured patients?
4. Is the ED on Consideration (C) or deferral from ambulances based on workload?
5. Weekday;
6. Weekend;
7. Time of day in 8 hour intervals (08:00-16:00, 16:00-24:00, 24:00-08:00);
8. Age (as a continuous variable);
9. Sex;
10. History of MI;
11. History of CABG;
12. History of angioplasty;
13. Location of STEMI (anterior, posterior, inferior);
14. Off load delay (minutes);
15. PCA or PCI or bypass surgery.

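### The symptom-onset-to-reperfusion interval, a secondary outcome, is compared across strategies without removing the delay before paramedics arrive, which no strategy can change

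*Protocol article*

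**What the plan says.** All references are to the protocol article.

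- **Outcome.** Treatment Time Intervals lists six secondary intervals. One is: "Symptom onset time interval defined as time from symptom onset reported by subject to reperfusion intervention". It ends at drug administration or balloon inflation. The other five start at scene arrival, at scene departure or at a hospital door.
- **Entry.** Under Inclusion criteria, patients are "Suspected by the paramedics to have ischemic chest pain for greater than 30 minutes but less than 6 hours".
- **Test.** Under Analysis Plan, the method is stated as follows: "The primary outcome, and treatment time intervals, will be analyzed with one-way ANOVA and subsequent pair-wise multiple comparison procedures across the four treatment strategies".
- **Adjustment.** "Different covariates (Table 3) will be analyzed using multiple linear regressions and they will be introduced into the model and evaluated as potential confounders". Table 3 has 15 entries: hospital and ED characteristics, calendar and clock time, age, sex, cardiac history, infarct location, off-load delay and procedure. None is symptom duration, onset-to-call time or onset-to-paramedic time.
- **Retention.** "Variables will be retained if they have had an effect of 5% or greater on the coefficients for door-to-reperfusion time".
- **How groups arise.** Study Design defines four strategies by ECG capability and bypass eligibility: "Bypass eligibility was based on transport distance of patients from their pick-up location to PCI center and the cut-off point was 60 kilometres". Setting describes the regions as "representing rural, suburban, urban, and metropolis areas".

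**The concern.** The interval is the sum of a part that no strategy can influence (onset to paramedic arrival) and a part that the strategies are meant to shorten (arrival to reperfusion). The planned analysis treats the sum as if all of it could respond to the strategy.

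The covariate step does not repair this. The delay is not a candidate. The retention rule looks at door-to-reperfusion time, whose clock starts after the delay has ended. Off-load delay, the only Table 3 item measured in minutes, occurs at the hospital.

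Groups are not randomised. They follow region and distance, and pre-contact delay includes both the patient's decision to call and the ambulance's travel to the scene. Balance between groups therefore cannot be taken for granted. At stake is the reading of the one listed interval that covers the whole path from onset to reperfusion, in a study whose Background gives reducing that time as its reason for comparing strategies.

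This is not a detail left to a later plan: the article itself names the test, the covariate list and a numerical retention rule.

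**Working it through.** **Plan's own figure.** The article gives no SD, effect size or power for this interval. Table 2 concerns the binary primary outcome. A continuity-corrected two-proportion formula (two-sided 0.05, 80% power) gives 402, 185 and 107 per arm against the stated 402, 185 and 106. Only the recruitment goal of 100 STEMI patients per group is carried forward.

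**Structure.** Let D be onset to paramedic arrival, S paramedic arrival to reperfusion, and T = D + S. Then:

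- contrast in mean T = contrast in mean S + contrast in mean D, so an imbalance in D enters with coefficient 1;
- Var(T) = Var(D) + Var(S) if D and S are independent;
- regressing T on strategy and D gives the same strategy coefficient as regressing S on strategy and D, because subtracting D from the outcome only lowers D's own coefficient by 1.

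**Assumed inputs.** SD(D) 50 to 95 min; a uniform spread over the 30 to 360 min window gives (360 − 30)/√12 = 95. SD(S) 40 to 90 min. D and S are independent, n = 100 per group, all reperfused, with one two-sided pairwise test at 0.05.

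**Precision.** Standard error = SD × √(2/100); power ≈ Φ(20/SE − 1.96) for a 20-min difference.

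| SD(D) | SD(S) | SD(T) | Power on T | Power with D removed |
|---|---|---|---|---|
| 50 | 40 | 64 | 60% | 94% |
| 50 | 60 | 78 | 44% | 65% |
| 50 | 90 | 103 | 28% | 35% |
| 75 | 40 | 85 | 38% | 94% |
| 75 | 60 | 96 | 31% | 65% |
| 95 | 40 | 103 | 28% | 94% |
| 95 | 60 | 112 | 24% | 65% |
| 95 | 90 | 131 | 19% | 35% |

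Worked row (50, 90): SD(T) = √(2500 + 8100) = 103, SE = 14.56, Φ(1.37 − 1.96) = 28%. With D removed, SE = 12.73 and Φ(1.57 − 1.96) = 35%.

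**Bias.** Suppose the strategies have no effect and mean D differs by 15 min. The expected contrast is then 15 min. The chance of declaring it significant is:

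- SD(T) 64: SE 9.06, 15/9.06 = 1.66, about 38%;
- SD(T) 112: SE 15.89, 15/15.89 = 0.94, about 16%;
- SD(T) 131, the widest case in the table: about 13%.

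**Simulation check.** With skewed delay (SD 60), SD(S) 45, no strategy effect and 1,500 runs each, shifts of 10, 20 and 30 min in D gave unadjusted contrasts of 10.8, 20.2 and 30.5 min, significant in 17%, 47% and 82% of runs. With D as a linear covariate the contrasts were within 0.3 min of zero and significant in 4% to 6%.

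**Form of the covariate.** D enters T linearly in minutes. Under skewed assumed delays with a 15-min shift, a linear term left essentially no bias. A log-only term left about −2 to −5 min, depending on the distribution assumed.

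**The case against.** Several objections have force.

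- **Scope.** Only one of six secondary intervals is touched. A reader might infer that the primary comparison is compromised. It is not: door-to-reperfusion time starts after the delay has ended.
- **Information already present.** It would be tempting to say that the plan cannot show the part the strategies act on. That goes too far. Scene time, transport time and the primary-hospital or PCI-transfer reperfusion interval are consecutive and together cover arrival to reperfusion. What is absent is that sum as one interval with its own test.
- **A different quantity.** Total time from onset matters in its own right, and the Background frames the study in those terms. Adjusting for D turns the contrast into one about arrival to reperfusion. This is a reason to keep reporting the total, not to attribute differences in patient delay to the strategies.
- **Conditional bias.** A reader might infer that the groups do differ in pre-contact delay. Nothing in the article says so. Age, sex and time of day may also be partial proxies, although they cannot be relied on to remove an additive component.
- **Assumed size.** No SD, 20-min effect or 15-min imbalance comes from the article. Large power gains depend on SD(S) being small, yet S mixes fibrinolysis, direct PCI and inter-hospital transfer and could vary widely. The single 0.05 test also ignores the planned multiple-comparison procedures.

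The objections limit reach and size. They leave standing the mismatch between this outcome and the analysis specified for it.

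**Conclusion.** The point holds for the symptom-onset-to-reperfusion interval alone. As specified, its strategy contrast absorbs any between-group difference in pre-contact delay in full, and its error variance includes the spread of that delay. The first effect needs an imbalance, which the article neither reports nor excludes. The second arises without one.

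The mechanism is arithmetic; the size is not established. Across the assumed SDs the precision gain runs from 7 percentage points of power (28% to 35%) to 66 (28% to 94%), so no single figure should be cited as the loss. The 16% to 38% spurious-significance range likewise depends on an assumed 15-min imbalance and total SDs of 64 to 112 min. The documents do not support extending the point to the primary outcome, and no case is made for extending it to the Cox model for survival.

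**What to change.** In the Analysis Plan, keep total onset-to-reperfusion time as a reported outcome, but base its strategy contrast on one of the following:

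1. a model that includes onset-to-paramedic-arrival time as a linear term in minutes, or a spline that contains the linear term, forced in and exempt from the 5% rule; or
2. paramedic arrival at scene to first reperfusion, listed and tested as one summed interval under Treatment Time Intervals. This targets the same contrast when arrival-to-reperfusion time does not itself depend on the earlier delay.

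Do not use a log term alone. Leave the primary-outcome and Cox models as they are on this point.

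The cost is a few lines of wording and one derived variable. Onset time and scene arrival already define listed intervals, so no new data or patients are needed. Reported onset is imprecise and will be missing for some patients, which affects option 1, but the existing outcome already shares that weakness. Option 2 does not use onset time at all.

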### Access to Interventions

The rate of reperfusion strategy utilization across groups including fibrinolysis, percutaneous coronary angiography and intervention, coronary artery bypass surgery, bypass to PCI centre directly vs. transfer from a non PCI centre.

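### One-way ANOVA on the pooled primary hospital reperfusion interval cannot separate speed of treatment from the fibrinolysis/PCI mix

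*Protocol article*

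**What the plan says.** Under Primary Outcome the protocol article keeps the two treatments on separate clocks: "Target door to reperfusion times are 90 minutes for primary PCI intervention (door-to-balloon time) and 30 minutes for fibrinolysis (door-to-needle time").

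Under Treatment Time Intervals it does not. The primary hospital interval runs from arrival to "reperfusion intervention at the primary destination (defined as time to drug administration or balloon inflation"), a single continuous variable. The PCI-transfer and PCI-site intervals carry the same parenthesis but end at the PCI site, for example "PCI site reperfusion time interval defined as the time from arrival at PCI site to reperfusion intervention at the PCI site".

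The Analysis Plan states: "The primary outcome, and treatment time intervals, will be analyzed with one-way ANOVA and subsequent pair-wise multiple comparison procedures across the four treatment strategies". It then adds a regression step: "Different covariates (Table 3) will be analyzed using multiple linear regressions and they will be introduced into the model and evaluated as potential confounders". Covariates stay in the model if they move the door-to-reperfusion coefficients by at least 5%.

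Under Study Design, strategy 4 is "12-lead PHECG with prehospital notification and eligible for bypassing the nearest receiving ED with transport to a PCI center". Strategies 1 to 3 go to the nearest ED; strategy 1, for instance, is "3-lead PHECG and transported to the nearest receiving ED who were not eligible for bypass based on transport time". Access to Interventions makes the treatment mix an outcome in its own right: "The rate of reperfusion strategy utilization across groups including fibrinolysis, percutaneous coronary angiography and intervention".

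**The concern.** A reader will take a comparison of door-to-reperfusion intervals as an answer to whether a strategy delivers treatment faster after arrival. The mean of a pooled interval is a weighted average of the needle mean and the balloon mean, and the weights are the shares of patients receiving each treatment. If the shares differ by strategy, the means differ even when every strategy is equally quick at each treatment. The protocol expects the shares to differ, because destination differs by strategy and the mix is itself compared.

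A bypass strategy that moves patients from fibrinolysis to PCI could therefore be reported as significantly slower although its door-to-needle and door-to-balloon times are the same as elsewhere, or better. That result would sit beside a primary outcome judged on treatment-specific targets, and the two could point in opposite directions.

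**Working it through.** **Plan's own figures.** The protocol gives no sample size, SD or expected mean for the intervals. Table 2 concerns the binary primary outcome. With two-sided alpha 0.05, 80% power and a continuity correction, its three rows reproduce as 402, 185 and 107 per arm (printed: 402, 185, 106). Nothing there bears on the intervals.

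**Step 1: what the ANOVA compares.** Let p be the PCI share of a strategy within the interval:

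pooled mean = (1 − p) × needle mean + p × balloon mean.

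If needle and balloon means are the same in two strategies, the difference in pooled means is (p₂ − p₁) × (balloon mean − needle mean). It is zero only if the shares or the two treatment means are equal.

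**Step 2: conflict with the primary outcome.** Suppose every balloon in one group is at 80 minutes and every needle in another is at 40. On the primary outcome the first group is 100% on target (80 < 90) and the second 0% (40 > 30). On the pooled mean the first looks 40 minutes slower.

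**Step 3: size from the protocol's planning rates.** Sample Size Calculation cites baseline rates of 31% lysed within 30 minutes and 29% with PCI within 90. Assuming lognormal times with log-SD s, median = target / exp(s × z), where z(0.31) ≈ −0.496 and z(0.29) ≈ −0.553.

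- s = 0.5: needle 38.4 min, balloon 118.7 min.
- s = 0.7: needle 42.4 min, balloon 132.6 min.

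At s = 0.5, mean = median × exp(0.125), giving about 43.5 and 134.5 min. Moving from 20% to 80% PCI shifts the pooled mean by 0.6 × (134.5 − 43.5) ≈ 55 min with no change in speed. The on-target proportion barely moves: 0.8 × 31% + 0.2 × 29% = 30.6%, against 0.2 × 31% + 0.8 × 29% = 29.4%.

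**Step 4: how often the ANOVA rejects when no strategy is faster.** Four groups of 100 reperfused patients, identical needle and balloon distributions in all four, 1,500 runs per scenario, alpha 0.05. Only the PCI share varies (strategies 1/2/3/4). Each cell gives log-SD 0.5, then 0.7.

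| Needle / balloon medians (min) | 30/30/30/30% | 20/30/20/30% | 20/40/20/40% | 20/40/20/80% |
|---|---|---|---|---|
| From planning rates (step 3) | 5%, 5% | 22%, 15% | 71%, 51% | 100%, >99% |
| 30 / 90 | 5%, 5% | 24%, 13% | 73%, 49% | 100%, 99% |
| 45 / 75 | 6%, 5% | 11%, 8% | 29%, 15% | 97%, 69% |

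Medians, log-SDs, shares and 100 reperfused per group are all assumptions. At 60 per group the effect persists but is smaller.

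**Step 5: the direction can reverse.** Medians 40 and 90 min, log-SD 0.6, so means are 40 × exp(0.18) ≈ 47.9 and 90 × exp(0.18) ≈ 107.7.

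- Strategy with 20% PCI: 0.8 × 47.9 + 0.2 × 107.7 ≈ 60 min.
- Strategy 20% faster at both treatments, with 80% PCI: 0.8 × (0.2 × 47.9 + 0.8 × 107.7) ≈ 77 min.

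The strategy that is faster at each treatment has the longer mean.

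**Step 6: what a treatment indicator does.** With a true fibrinolysis/PCI indicator in the model, the strategy test rejects in 4–6% of runs in every scenario above. At a more extreme mix (10/30/10/95%) it rejects in 5–8%, because the variances are unequal.

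**The case against.** Several points on the other side have weight.

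- **The plan does adjust.** A reader might infer that nothing is done about the mix. That is not so: Table 3 covariates enter a linear regression, including item 1 (24-7 PCI-capable laboratory at the primary destination) and item 15 (PCA, PCI or bypass surgery grouped together). With a strongly unequal mix, such a term would be expected to pass the 5% rule. This stands as partial mitigation. The regression is separate from the ANOVA and retention is data-driven. Item 1 describes the hospital. Item 15 does not identify fibrinolysis as the reperfusion treatment, so a lysed patient with later angiography could be coded with primary PCI patients.
- **Not every interval is exposed.** The PCI-transfer and PCI-site intervals probably hold mostly balloon times, although their definitions still admit drug. The symptom-onset interval is legitimately a total delay. The point falls mainly on the primary hospital interval.
- **A difference due to mix is real.** Mix is a consequence of strategy, so if bypass moves patients to a treatment that takes longer, mean time to reperfusion does differ. Calling every such rejection false goes too far. The ANOVA answers a total-effect question; it does not answer which strategy treats faster.
- **The simulated structure is simplified.** The plan enrols 100 STEMI patients per group, and not all will be reperfused. Patients transferred for PCI fall outside the primary hospital interval, so its mix is not the group's overall mix. This limits the rates, not the mechanism.
- **This could be left to an analysis plan.** Presentation by treatment might be. But the article itself states both the pooled definition and the test.

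A reader might also infer that the economic analysis inherits the problem. Economic Outcomes and the Analysis Plan refer to door-to-reperfusion time and a time-to-reperfusion interval without saying which defined interval is meant, so this is not established.

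**Conclusion.** The point holds for the primary hospital reperfusion interval. As written, its one-way ANOVA mixes treatment mix with speed. It can reject when no strategy differs in door-to-needle or door-to-balloon time, can favour the slower strategy, and can point against the primary outcome.

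The mechanism follows from the protocol's definition, its test, its two targets and its destination rules. The size does not: rejection ranged from about 8% to 100% at unequal mix, depending on assumed shares, medians, spread and number reperfused, none of which the documents give. It is near certain only when the mix differs strongly, which the bypass design makes plausible.

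The documents do not support extending the point to the primary outcome, which applies treatment-specific targets and does not share the defect in this form. This is a secondary outcome and worth correcting, but it does not threaten the main comparison.

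**What to change.** In Treatment Time Intervals and the Analysis Plan:

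1. Analyse the primary hospital interval separately as door-to-needle (fibrinolysis) and door-to-balloon (primary PCI), the terms Primary Outcome already uses. Alternatively, stratify by an indicator of fibrinolysis versus primary PCI as the reperfusion treatment, included by rule and not subject to the 5% retention criterion.
2. Report these results beside the proportion receiving each treatment by strategy, which Access to Interventions already plans.
3. Keep the pooled interval as a descriptive measure of total delay after arrival.

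The cost is a wording change and a few more tables; both treatment times are already within the interval's definition. Each stratum will be smaller, with wider confidence intervals. The separate results are conditional on treatment received, which itself follows from strategy, so they must be read with the treatment-mix table and not as unconfounded effects of strategy.
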